### Video design

A video will be designed and made by a professional company under the supervision of three experts from the China Centers for Disease Control and Prevention (CDC) and university hospitals. They will help us check the content of the video. A pilot test will be performed to determine the understanding of older adults. Eventually, the video content will consist of 1) influenza knowledge, which covers symptoms, complications, transmission routes, treatment measures, and prevention. 2) influenza vaccine knowledge, including types of vaccine, time of injection, health benefits, and 3) influenza pandemic cases globally.

### Data collection instrument

A questionnaire-based on the Health Belief Model (HBM) has been developed after a literature survey [18, 33–37]. A panel comprising three experts on public health and ten older adults established the content and face validity of the questionnaire. Thirty older adults were recruited in the pilot testing, and the questionnaire was administered over the telephone by medical students. The reliability of the final form of the questionnaire was assessed by measuring the value of Cronbach’s alpha, which was excellent (Cronbach’s alpha = 0.844).

The questionnaire consisted of four sections, including basic sociodemographic characteristics, knowledge part, attitude part, and behavior part (supplementary file). Gender, age, occupation, education, monthly income, and chronic disease were listed in the sociodemographic part. There were 10 true or false questions regarding influenza and influenza vaccine in the knowledge part with yes, no, and unclear options. The knowledge score will be calculated using correct answers with a maximum score of 10 points. Moreover, the knowledge of the participants will be categorized into three classes, such as poor (< 4 points), average (4–7 points), and good (> 7 points).

Eight questions were asked to explore the attitude about the risk of influenza infection, the burden of disease, safety, effectiveness, and treatment. Here, the Likert scale was used to get an attitude score. Hence, 40 points are as full scores (strongly agree-1 point, agree-2 points, uncertain-3 points, disagree-4 points, and strongly disagree-5 points).

Six practice-related questions were designed to determine the behavior of prevention about influenza treatment in influenza-like illness (ILI), willingness to accept the vaccine. The practice score, a maximum of 12 points, will be calculated based on the response of participants (yes-1 point, no-2 points).

### Intervention procedures

The medical students will be recruited from high grades in medical colleges. Screening criteria include 1) those who are well versed in information about various diseases and vaccination; 2) those who could have a better understanding of our study protocol; 3) those who like to educate older adults. Before the formal investigation, medical students will be provided four hours of focused training to increase their understanding of influenza, influenza vaccination, questionnaire items, and video-related professional knowledge. Additionally, a session of training will also be conducted to improve their communication skills, which will help them to better communicate with older adults. The training adequacy of medical students will be conducted through group discussions during which they will be asked to comment directly on their readiness to play their defined role. Any component of the training that will be considered insufficient would subsequently be addressed.

Before the intervention, medical students will call the older adults, enquiring about their willingness to participate in this program. After their verbal agreement, older people in the control and intervention group will fill the questionnaires under the supervision of a medical student. Their knowledge, willingness to accept the vaccine, and uptake rate will be assessed.

Formal intervention contains two phases. The first to the third month is the first phase, and the fourth to the sixth month is the second phase. During the first to the second month, the educational intervention and basic health check will be provided to the intervention group in the community hospitals. Initially, a basic health check will first be conducted for participants by medical students. Next, they will be taken to a comfortable room, where a 12 min video will be broadcasted. Then, medical students will answer older adults regarding questions or doubts about the video or influenza vaccine in the next 15 min through a small discussion group. One medical student will be responsible for educating 5 older adults, making them understand the video’s content fully. To guarantee that the older adults actively participate in the discussion, a small gift like a toothbrush will be prepared for them. In contrast, only basic health checks in the control group will be done. In the third month, medical students will make a telephonic call to all enrolled participants to fill in the questionnaire. Then, from the fourth to the sixth month, the procedure will continue as described previously (Fig. 1). After the intervention, effectiveness will be assessed by information collected.

**Fig. 1 Fig1:**
[figure not shown]
Process of intervention

### Outcome indicators

The primary outcomes are willingness to accept influenza vaccination and vaccination coverage, which will be assessed through their self-report. The secondary outcomes are knowledge, attitude, and behavior scores.

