**Methods:**

A cluster randomized controlled trial will be conducted in 4 districts of Xi’an city, Shaanxi Province, China, using a stratified sampling approach. Adults aged ≥60 years will be recruited from 8 community hospitals. A self-administered questionnaire of knowledge, attitudes, and practices (KAP) will be employed to record the KAP score. During the 6-month interventional period, participants in the intervention group will receive educational videos focused on influenza and influenza vaccination, coupled with a group discussion conducted by the medical students. For those in the control group, no intervention will be provided. The outcomes measured in both groups will be the influenza vaccination coverage and the KAP scores of all participants.

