### Sample size

According to previous studies [31], the influenza vaccine coverage among older adults was almost 2% in western China. The relative risk of intervention ranged from 1.04 to 6.22 in the uptake rate compared to the control group. We hypothesized that the influenza vaccine’s uptake rate would increase from 2 to 10% by employing a medical student-led educational intervention. A mathematical formula [32] was used to calculate the minimum sample size. Eighty participants will be required for each group with a study power of 0.90 and a significance level of 0.05. Considering the loss of follow-up and the low response rate, the sample size will be 200 participants for one group.

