### Data analysis

Epidata 3.1 will be employed to input data with the help of two investigators. All data collected will be stored on a password-protected computer. Descriptive statistics will be used to present the sociodemographic characteristics of the participants as mean ± standard deviation (M ± SD) and percentage. The chi-square test will be used to compare the difference between vaccination uptake and the correct knowledge rate between the intervention group and the control group before and after the intervention. The t-test will be employed to check the difference in scores of knowledge, attitude, and behavior. A significance level of 5% will be selected in every estimate. The SPSS version 21.0 will be used to perform all analyses.

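### Two unranked primary outcomes, each at 5% in a trial sized on uptake alone, allow a false primary claim rate of up to 9.75% and a success on stated willingness without more vaccination

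*Protocol article*

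**What the plan says.** Outcome indicators names two primary outcomes in one sentence: "The primary outcomes are willingness to accept influenza vaccination and vaccination coverage, which will be assessed through their self-report". It does not put one before the other, and it does not say whether one significant result is enough or both are needed. The knowledge, attitude and behaviour scores are secondary.

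Data analysis gives one rule on error: "A significance level of 5% will be selected in every estimate". It names a chi-square test for uptake and for the correct-knowledge rate, and a t-test for the scores. It names no test for willingness.

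Sample size concerns uptake only. The hypothesis is that the "uptake rate would increase from 2 to 10" per cent. On that basis, "Eighty participants will be required for each group with a study power of 0.90 and a significance level of 0.05", raised to 200 per group for losses and low response. No rate or effect is given for willingness.

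The Abstract states the aim as raising vaccination coverage in adults aged 60 and over. The Background closes with improved knowledge and greater uptake as the aims. Neither statement makes willingness an aim.

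**The concern.** Two primary outcomes without a combining rule leave the definition of a positive trial open until the results are known. A flat 5% for every estimate means that no allowance is made for the two chances.

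The two outcomes also differ in kind. Coverage is what the trial aims to change and what it was sized for. Willingness is a stated intention, reported by the participant. The medical students who deliver the education also make the month-3 questionnaire call. An answer about intention can move without any change in vaccination. As the text stands, higher willingness with flat coverage could be reported as success on a primary outcome, and a health authority could take that as evidence that the programme raises vaccination.

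**Working it through.** **Inputs.** Two primary outcomes (Outcome indicators). 5% per test, unadjusted (Data analysis). Uptake of 2% against 10%, power 0.90, level 0.05, 80 per group before and 200 after the allowance for losses (Sample size). The documents do not state sidedness, so two-sided tests are assumed. They also do not state the correlation between the two test statistics, so a range is shown.

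**The plan's own figure.** With the usual pooled formula,

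n = [z(0.975)·√(2·p̄·(1−p̄)) + z(0.90)·√(p1(1−p1) + p2(1−p2))]² / (p2−p1)²

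and p̄ = 0.06:

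- first term: 1.960 × √0.1128 = 0.658
- second term: 1.282 × √0.1096 = 0.424
- n = (0.658 + 0.424)² / 0.0064, which rounds up to 184 per group (calculated without intermediate rounding).

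The stated 80 is not reproduced. It is a separate matter, and nothing below depends on it.

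**Family-wise error if either outcome is enough.**

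- Independent tests: 1 − (1 − 0.05)² = 0.0975, or 9.75%.
- Bound under any dependence: 0.05 + 0.05 = 10%.
- Positively correlated normal test statistics, by simulation with 1,000,000 draws per setting:

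| Assumed correlation | Family-wise error |
|---|---|
| 0.3 | 9.5% |
| 0.5 | 9.1% |
| 0.7 | 8.3% |
| 0.9 | 7.0% |

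The rate stays above 5% throughout. Counting only false claims in favour of the intervention, the nominal rate is 2.5% per test, and two independent tests give 1 − 0.975² = 4.9%. The relative inflation is about the same.

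**If both outcomes were required.** The error rate would not inflate. Power would be no greater than the power for coverage alone, and it cannot be calculated because no rate is given for willingness.

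**Cost of splitting alpha instead.** At 0.025 per outcome the same formula gives 217 per group against 184. With 200 analysed per group, power for coverage falls from 92.4% to 87.4%. These figures are before clustering and losses. Naming one primary outcome, or testing the two in a fixed order, keeps coverage at the full 5% and avoids this cost.

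**The case against.** The strongest reply is that the inflation assumes an either-or rule that the article never states. How two primary outcomes combine is often left to the analysis plan, which is not shown. The article is condensed, and its Discussion calls the study exploratory. It also names no test for willingness, so a 5% test of that outcome is inferred from the general sentence. This has force: 9.75% is conditional, not a rate to which the plan commits itself. But the article does more than stay silent. It makes both outcomes primary and fixes 5% for every estimate, so a later plan that divided alpha would depart from it. The mismatch with the sizing and the aim stands in any case.

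Some stronger readings are tempting but not supported:

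- **Four tests and 18.5%.** The plan has an interim contact: "In the third month, medical students will make a telephonic call to all enrolled participants to fill in the questionnaire". A reader might infer two outcomes at two time points and 1 − 0.95⁴ = 18.5%. But Intervention procedures places the judgement of effectiveness after the intervention, Data analysis compares the groups before and after it, and Study design gives it six months. Nothing says that month-3 data are tested as a primary result. The second follow-up questionnaire is itself inferred from the statement that the procedure continues.
- **The Abstract contradicts the primary outcomes.** It says "The outcomes measured in both groups will be the influenza vaccination coverage and the KAP scores of all participants" and does not name willingness. But it labels nothing primary or secondary, and willingness is among the practice questions that the KAP scores cover.
- **The month-3 call comes too early for coverage.** It falls in October, while vaccination continues through the season. That would matter only if month 3 decided the result, which the text does not say.
- **Double counting.** The practice questions include "willingness to accept the vaccine", so one answer may inform a primary outcome and a secondary score. That is not an error in itself.

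**Conclusion.** The point holds in a limited form. The article leaves two primary outcomes unranked, sets an unadjusted 5%, and is sized for one of them. If either outcome alone can make the trial positive, the rate of false primary claims is up to 9.75% under independence and about 7.0% to 9.5% at assumed correlations of 0.9 to 0.3. This assumes two-sided tests, a test of willingness at 5%, and one comparison per outcome after the intervention. It takes no account of clustering within the eight hospitals, which is a separate question.

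The larger consequence is interpretive: a gain in willingness without a gain in vaccination could count as primary success in a trial that aims to raise coverage. This should be settled before outcomes are compared by group.

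**What to change.** Name one primary outcome: cumulative vaccination coverage at the end of the six-month intervention, counting a participant as vaccinated if vaccinated at any time since baseline, tested at 5%. Make willingness and any month-3 results secondary, and say so in Outcome indicators and Data analysis.

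If both outcomes must stay primary, fix the order: test coverage at 5%, and test willingness at 5% only if coverage is significant. This holds the family-wise error at 5% without splitting alpha.

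The practice score can stay as designed, so the piloted questionnaire need not change. The cost is revised outcome wording and a registry update, with no extra participants. What is given up is that willingness can no longer carry a positive claim alone.

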### Randomization

All community hospitals in the four districts will be numbered. Then using computer-generated random numbers, community hospitals will be chosen at random. We will use the community health records management system of Xi’an city to export older adults’ health information of community hospitals and order from 1 to n. Corresponding older people through random number software generating 400 numbers will be selected as a sample. After the older adults are recruited, medical students will choose eligible participants and complete informed consent. Using the knowledge, attitudes, and practices (KAP) questionnaire, baseline information will be collected. On account of balancing the baseline, the clusters will be grouped in the intervention and control group randomly through randomization design and Chi-square test.

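### Vaccination coverage, the primary outcome behind the sample size, rests on unverified self-report in a trial where participants can tell their arm, so a modest difference in over-reporting between arms could look like an effect

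*Protocol article*

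**What the plan says.** Under Outcome indicators the article names two primary outcomes: willingness to be vaccinated and "vaccination coverage, which will be assessed through their self-report". Coverage is the outcome used under Sample size, where the background figure is that "the influenza vaccine coverage among older adults was almost 2% in western China" and the hypothesis is that the "uptake rate would increase from 2 to 10% by employing a medical student-led educational intervention". Data analysis compares uptake between groups by chi-square test, and Economic evaluation takes the gain in uptake as its health effect.

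Under Intervention procedures, medical students run the video session and then a 15-minute discussion, one student to five participants, with a small gift to encourage participation. In that discussion "medical students will answer older adults regarding questions or doubts about the video or influenza vaccine". Controls receive the basic health check alone. In the third month "medical students will make a telephonic call to all enrolled participants to fill in the questionnaire", and months four to six repeat the procedure. Medical students also make the recruitment call and supervise the baseline questionnaire in both arms.

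The article names no other source for vaccination status. Under Randomization, the trial uses the city's community health records system to "export older adults’ health information of community hospitals", but only to draw the sample.

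**The concern.** Vaccination is a dated event that can be confirmed, yet the article fixes the participant's own word as the way to measure it. Intervention participants have watched a video and held a discussion that favour vaccination. They are then asked about vaccination by a member of the same professional group that taught them. Controls have had no teaching. A wish to give the approved answer is therefore likely to be stronger in the intervention arm, and nothing in the comparison would cancel the difference.

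The low expected coverage makes this matter. At about 2% true coverage, some 98% of participants are in a position to give a false positive answer, so a small false-report rate can outnumber the true vaccinations. A larger sample does not help, because it makes a biased difference more likely to be significant. Any error passes into the chi-square test and the cost-effectiveness ratio alike.

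**Working it through.** **Inputs from the article.** Control coverage 2%; hypothesised intervention coverage 10%; 5% significance level; power 0.90; minimum 80 per group, raised to 200 per group (Sample size). Chi-square comparison (Data analysis).

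**Assumed input.** f is the share of unvaccinated participants who falsely report vaccination. The article gives no value, so a range is shown. Clustering by hospital is ignored throughout.

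**The plan's own figure.** The article states: "Eighty participants will be required for each group with a study power of 0.90 and a significance level of 0.05". The usual two-proportion formula, two-sided, gives

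n = [1.96·√(2·0.06·0.94) + 1.2816·√(0.02·0.98 + 0.10·0.90)]² / 0.08² = 183.1, i.e. 184 per group.

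The one-sided version gives 150. The stated 80 is not reproduced. That is a separate matter and the present point does not depend on it; the calculations below use the planned 200 per group.

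**Step 1: observed coverage.** With true coverage p, observed coverage = p + (1 − p)·f. With p = 0.02 in both arms (no real effect) and accurate control reports:

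- f = 2%: 0.02 + 0.98·0.02 = 4.0%
- f = 5%: 0.02 + 0.98·0.05 = 6.9%
- f = 0.08/0.98 = 8.2%: 10.0%, equal to the hypothesised rate. This is about 16 of the 196 unvaccinated people in a group of 200.

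**Step 2: chance of a significant result with no true effect.** For observed rates a (control) and b (intervention), p̄ = (a + b)/2 and n = 200:

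chance = Φ{ [(b − a) − 1.96·√(2p̄(1 − p̄)/n)] / √([a(1 − a) + b(1 − b)]/n) }

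For a = 0.02 and b = 0.10 this is (0.08 − 1.96·0.02375)/0.02341 = 1.43, and Φ(1.43) = 0.92.

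| False reports, control | False reports, intervention | Observed coverage | Chance of p < 0.05 |
|---|---|---|---|
| 0% | 1% | 2.0% vs 3.0% | 9% |
| 0% | 2% | 2.0% vs 4.0% | 21% |
| 0% | 5% | 2.0% vs 6.9% | 66% |
| 0% | 8.2% | 2.0% vs 10.0% | 92% |
| 2% | 10% | 4.0% vs 11.8% | 83% |
| 5% | 10% | 6.9% vs 11.8% | 39% |
| 5% | 14% | 6.9% vs 15.7% | 80% |

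A simulation of the uncorrected chi-square test (200,000 runs, accurate control reports) gave 20%, 69% and 95% at f = 2%, 5% and 8.2%. With no false reports in either arm it gave about 4.5%.

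**Step 3: in head counts.** Suppose 4 of 200 controls and 12 of 200 intervention participants report vaccination. The pooled rate is 16/400 = 0.04, and z = 0.04/√(0.04·0.96·2/200) = 2.04, so p is about 0.04. If only four of the twelve were truly vaccinated, eight false reports make the result significant.

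**The case against.** The strongest reply is that the article is silent on who calls whom. It says medical students telephone participants, not that they telephone their own pupils, and it does not say who collects data after month six. Call rosters, scripts and masking of callers are details that a condensed article may leave to the full protocol. This stands: a reader might infer that participants report to the very student who taught them, but the text does not support that. It does not remove the point, because the choice of self-report is stated in the article itself.

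Second, a reader might infer that over-reporting affects one arm only. That is not supported either. Controls also deal with medical students, at the recruitment call, consent, baseline questionnaire and follow-up call, and may over-report too. Only the difference between arms counts, which is why the table includes rows with control error.

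Third, 8.2% was found by solving backwards for the hypothesised effect, and it assumes perfectly accurate control reports. That is correct. It is a benchmark, not an estimate.

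Fourth, nothing shows that the records system holds vaccination entries, and the Discussion notes that people in most places pay for the vaccine themselves, so complete recording cannot be presumed. This limits the remedy, not the concern. Finally, willingness, the other primary outcome, can only be self-reported and is unaffected by a records check.

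**Conclusion.** The concern holds as a risk of differential bias built into a stated method. One of two primary outcomes, and the one that sets the sample size, is measured only by unverified self-report in a trial whose participants can tell their arm. That last point is inferred from the contrast between video plus discussion and a health check alone.

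Under the stated assumptions (2% true coverage in both arms, 200 per group, clustering ignored), a false-report rate of 5% in the intervention arm against none in controls gives about a 66% chance of a false significant result. A rate of 8.2% reproduces the whole hypothesised effect, with about a 92% chance. If both arms over-report, at 5% and 10%, the chance is about 39%.

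A reader might go further and conclude that over-reporting will produce the effect, or that a positive result would carry no information. The article gives no misreporting rate, so neither follows. What follows is that a positive result on self-report alone would remain open to this explanation. The change should be made, but the trial is not unworkable without it.

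**What to change.** 1. Define the coverage outcome as vaccination confirmed by the same procedure in both arms. Use the community hospital or health-record entry where available, or otherwise a vaccination certificate. This assumes that the records system holds or links to vaccination entries and that consent covers the look-up. Keep self-reported vaccination as a supportive outcome; willingness stays self-reported.
2. Roster the existing students so that none calls participants from a hospital where they taught, and use a fixed script that asks for the date and place of vaccination.

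**Cost.** A modest look-up for about 400 people, a line in the consent form and a changed roster, with no extra staff. Doses given outside the recorded system may be under-captured where no certificate can be shown. The roster change reduces the bias but does not remove it, because participants remain unblinded and a caller who knows the hospital may infer the arm. It would still help if the records proved unusable.
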